## Abstract

**Background:**

In many health systems, specialist services for critically ill children are typically regionalised or centralised. Studies have shown that high-risk paediatric patients have improved survival when managed in specialist centres and that volume of cases is a predictor of care quality. In acute cases where distance and time impede access to specialist care, clinical advice may be provided remotely by telephone. Emergency retrieval services, attended by medical and nursing staff may be used to transport patients to specialist centres. Even with the best quality retrieval services, stabilisation of the patient and transport logistics may delay evacuation to definitive care. Several studies have examined the use of telemedicine for providing specialist consultations for critically ill children. However, no studies have yet formally examined the clinical effectiveness and economic implications of using telemedicine in the context of paediatric patient retrieval.

**Methods/Design:**

The study is a pragmatic, multicentre randomised controlled trial running over 24 months which will compare the use of telemedicine with the use of the telephone for paediatric retrieval consultations between four referring hospitals and a tertiary paediatric intensive care unit. We aim to recruit 160 children for whom a specialist retrieval consultation is required. The primary outcome measure is stabilisation time (time spent on site at the referring hospital by the retrieval team) adjusted for initial risk. Secondary outcome measures are change in patient’s physiological status (repeated measure, two time points) scored using the Children’s Emergency Warning Tool; change in diagnosis (repeated measure taken at three time points); change in destination of retrieved patients at the tertiary hospital (general ward or paediatric intensive care unit); retrieval decision, and length of stay in the Paediatric Intensive Care Unit for retrieved patients. The trial has been approved by the Human Research Ethics Committees of Children’s Health Services Queensland and The University of Queensland, Australia.

**Discussion:**

Health services are adopting telemedicine, however formal evidence to support its use in paediatric acute care is limited. Generalisable evidence is required to inform clinical use and health system policy relating to the effectiveness and economic implications of the use in telemedicine in paediatric retrieval.

**Trial registration:**

Australian and New Zealand Clinical Trials Registry ACTRN12612000156886.

## Background

In many health systems, specialist health services for critically ill children are organised regionally, typically in areas of high population. In this model, larger centres provide paediatric intensive care services and have ready access to a range of sub-speciality expertise. These specialist centres may also provide referring facilities with clinical advice by telephone and also contribute to, or be supported by, specialised paediatric patient retrieval services.

The clinical argument favouring regionalisation is that the concentration of expertise and resources, high patient volume and co-ordination of services within a geographic area leads to improved patient outcomes. [1] While a relationship between volume and outcome for children managed in paediatric intensive care units (PICU) has not been clearly established [2,3], studies have shown that high-risk paediatric patients have improved survival when managed in tertiary centres [4] and that volume of cases is positively associated with care quality [3]. It has also been shown that the centralisation of paediatric intensive care services, in combination with a specialised patient retrieval service, has clinical benefits [5]. There is also an economic argument for regionalisation: geographical factors and population distribution may dictate that regionalisation is the only affordable ways for a health system to provide complex specialist care. However, while the regionalised model may be both clinically beneficial and in some cases economically necessary, in urgent and emergent situations distance and time impediments may disadvantage those who live outside of the major centres of population.

When a critically ill child presents at a referring centre, the quality and timeliness of communication with clinicians at the specialist centre is very important. In this context, real-time telemedicine based consultations, alongside high-quality local care and a well-coordinated retrieval service, may have a useful role. It may be that consultation by telemedicine has advantages over use of the telephone arising from the ability to view clinically useful visual information, including directly observing the child, procedures, medical images and equipment such as the patient monitor output and ventilator settings.

The use of telemedicine is not new [6] and its potential role in paediatric critical care was first discussed by Wetzel in 2001 [7] at a time when the use of telemedicine in adult intensive care units (ICU) was still embryonic and PICU applications had yet to be developed. Subsequently, early studies of telemedicine for managing seriously ill children first began to appear in the literature in 2004, with the majority of the reported work being led by investigators at The University of California Davis (UCD). The first reported study examined the use of telemedicine to support the care of children admitted as inpatients in a remote adult ICU in Northern California [8]. This two year study, involving 70 consultations for 47 patients, found that children who received telemedicine consultations from a PICU at the UCD Medical Center (UCDMC) had mortality and length of stay (LoS) outcomes that were comparable to those of severity-adjusted reference benchmark data from 33 national PICUs. The study also reported that the referring clinicians and parents had high satisfaction with the use of telemedicine. Overall, the study suggested that it was feasible to provide quality care to some children in the community hence avoiding transport and inconvenience for families. The investigators also conducted an economic analysis [9] which reported annual hospital and transport savings of USD172,000 for patients who received telemedicine consultations and USD300,000 for patients who received telemedicine consultations and for whom transport was determined to be avoided. By retaining patients in the adult ICU, the referring hospital also increased their annual revenue by USD186,000 for patients who received telemedicine consultations and USD279,000 for patients for the patients who received telemedicine consultations and for whom transport was avoided. The annual cost of providing telemedicine was reported as USD120,000 economic benefit.

Also in 2004, Marcin et al. reported a second study of telemedicine consultation. [10] In this study 17 paediatric trauma patients who had been admitted to the same remote adult ICU were recruited. Telemedicine consultations were provided from UCDMC at the discretion of the referring clinician. This study also concluded that the approach was feasible for trauma care and was considered satisfactory by the referring clinicians and families. In 2005, Kon and Marcin reported two case studies of the use of telemedicine to support paediatric resuscitation [11]. In these examples, an intensivist observed and provided advice by telemedicine from home. While in one case resuscitation was ultimately unsuccessful, the attending teams reported that telemedicine had benefits because the intensivists could directly observe cardio-pulmonary resuscitation, bagging and the patient monitor and recommend interventions based on visual information that would not be available during a telephone call.

Between 2006 and 2008, Health et al. conducted a two year prospective study of intensivist telemedicine consultations to rural emergency departments (ED). [12] They reported the results of 63 consultations conducted across 10 rural EDs. Six point questionnaires were used to survey clinician opinions of telemedicine. The majority of both referring and providing clinicians agreed, or strongly agreed (referring 87.5%, providing 88.9%), that telemedicine improved the quality of care for the patient. Referring and providing clinicians differed in their views of whether the consultation could have been conducted as well by telephone, with 55% of referring clinicians disagreeing, or strongly disagreeing with the statement, compared with 90.5% of providing clinicians. Opinions on the technical quality of the consultations and on the quality of clinician communications were comparable between referring and providing clinicians, with the majority agreeing or strongly agreeing that the quality was high.

In 2012, Yager at al. examined the use of telemedicine for providing night-time consultations by intensivists to a PICU from home. [13] This descriptive retrospective study reviewed the audio and video quality, duration, reason for consultation, persons present and changes in medical management for 56 out-of-hours consultations. The study concluded that the use of telemedicine was feasible and valuable, though the effect on patient outcomes was not assessed.

In 2013 using a retrospective chart review, LaBarbera et al. identified that telemedicine consultations between intensivists and a community hospital physicians, together with the implementation of a paediatric hospitalist program at the community hospital had the potential to reduce the need for patient transport to the PICU. [14] Also using retrospective chart review, a validated implicit quality review tool and surveys, Dharmar et al. compared the quality of care provided to children who received a telemedicine consultation with a paediatric intensivist, a telephone consultation with a paediatric intensivist or no paediatric intensivist consultation at all. The study found that patients who received telemedicine consultations had the highest quality of physician-reported quality of care, intermediate quality was reported for telephone consultations and the lowest quality was reported for no intensivist consultation. [15] Dharmar et al. also compared medication errors in groups of children who received telemedicine consultations, telephone consultations or no consultation. The children who received telemedicine consultations experienced significantly fewer physician-related medication errors (3.4%) compared with those who received telephone consultations (10.8%) or no consultations at all (12.5%) [16].

In general, while telemedicine is not new, the formal evidence to support its use remains weak. [17] While pragmatic randomised controls may are a useful method of producing evidence for clinicians and policy-makers, very few have been published in telemedicine. In paediatric critical care specifically, there is very limited high-quality evidence. In their 2012 systematic review and meta-analysis, Wilcox et al. [18] identified no randomised studies of telemedicine in critical care. In their pooled analysis of 9 observational studies they found that the use telemedicine was associated with a reduction in ICU and hospital mortality (RR 0.79; 95% CI 0.65 to 0.96 and RR 0.83 95% CI 0.73 to 0.94 respectively). However, the pooled analysis included only one study of paediatric patients (Marcin et al. [8]) and that study favoured the control over telemedicine and had a wide confidence interval (RR 1.06, 95% CI 0.13 to 8.87). Wilcox also found that telemedicine was associated with a statistically significant reduction in LoS (both in ICU and in hospital) however no studies involving paediatric patients were reported in the pooled estimates.

While observational studies suggest that telemedicine may have clinical and economic benefits when compared with consultation by telephone, formal evidence is needed.

The aim of this study is to formally explore the clinical and economic effects of providing telemedicine consultations from a PICU to referring hospitals in Queensland’s regionalised public health care system.

### Objectives and hypotheses

#### Hypotheses

Consultation using real-time video-based telemedicine between a PICU consultant and a referring hospital clinician will:Clinical effectivenessReduce the time needed by the retrieval team to stabilise the child before transportImprove the child’s condition between time of initial call and time of retrieval team arrivalReduce diagnostic discordanceReduce the number of retrieved children being admitted to general wards at the tertiary hospitalReduce PICU LoS for retrieved childrenEconomic effectsFrom the health service perspective, be economically beneficial by reducing the number, and consequently the cost, of (i) retrievals, (ii) unnecessary tertiary hospital admissions, and (iii) LoS.

## Methods/Design

### Design

This study is a pragmatic four-centre open randomised controlled trial. Patients recruited to the intervention arm will receive a telemedicine consultation, while patients recruited to the control arm will receive a telephone consultation (usual care). The study will be conducted over 24 months.

This study is focussed on the role of telemedicine in the management paediatric retrievals and hence will randomise retrieval calls only, and have a retrieval-related primary outcome measure. However, information will also be collected for telemedicine-based clinical advice-only calls which are placed directly to the PICU and this information will be used for separate secondary observational analyses.

The study has been approved by the Queensland Children’s Health Services (RCH) Human Research Ethics Committee (HREC/11/QRCH/175) and The University of Queensland Medical Research Ethics Committee (2012000136). The study will be conducted in accordance with the principles of the Declaration of Helsinki and reported in accordance with the CONSORT statement.

### Setting

Queensland is Australia’s second largest state/territory with an area of over 1.7 million square kilometres. It has a population of over 4.5 million, has around 60,000 births per year and high population growth in regional areas. However, Queensland’s two tertiary children’s hospitals are both located in the state capital of Brisbane in the southeast corner of the state, in effect centralising speciality and sub-speciality care.

The Royal Children’s Hospital (RCH) PICU provides a state wide advice and retrieval service. Approximately 230 paediatric patients who need critical care are retrieved to the unit each year. Clinical advice and retrieval management between the PICU and referring hospitals is provided by telephone. First point of call, clinical co-ordination, prioritisation and tasking of resources for all paediatric retrievals is conducted centrally by Retrieval Services Queensland (RSQ) based at the Queensland Emergency Medical System Coordination Centre in Brisbane.

### Study site selection

The study is funded to provide the RCH PICU and four study sites with telemedicine equipment. To maximise recruitment within the resource constraints of the project, retrospective data were examined to identify four referring hospitals which consistently contributed to the PICU retrieval workload over two recent years (2010, 2011). For this period, when referring hospitals were ranked by retrieval activity, the top four hospitals accounted for 220 patients (i.e. approximately 110 patients per year). These cases represent almost half of the total retrieval workload of the PICU. These study sites are all large regional public hospitals, each with an emergency department, paediatric ward and paediatricians on staff. In some cases, adult ICUs at the referring hospitals may admit paediatric patients if needed. Site round trip distances from the RCH PICU range from 62 km to 1042 km (Table 1). The four sites identified will be provided with telemedicine links to the RCH PICU.

**Table 1 Tab1:** **Study sites, usual retrieval mode and round trip distance from the RCH**

**Study site**	**Usual mode of retrieval**	**Round trip distance**	
		**Air (nm; km)**	**Road (km)** ^**1,3**^
Redcliffe Hospital	Road ambulance	N/A^2^	62
Nambour General Hospital	Helicopter	100;185	N/A^2^
Bundaberg Base Hospital	Fixed wing aircraft	312;578	41
Rockhampton Base Hospital	Fixed-wing aircraft	562;1042	36.4

^1^Using main roads; ^2^Direct hospital-to-hospital; ^3^Fixed wing retrievals include road-ambulance components between the referring hospital and local airport, and between the Royal Children’s Hospital and the Royal Flying Doctor Service at Brisbane Airport.

### Participants

#### Patients

Study participants will be male or female children, aged 15 years or under, who are inpatients, or who present at the emergency departments of any of the four regional referring study hospitals and for whom a consultation with the tertiary PICU is required. Reasons for such consultations may be to seek clinical advice from the PICU, and/or to plan retrieval of the child. Informed consent will be obtained from a parent or guardian by a clinician at the referring hospital before recruitment. A patient information sheet and consent form will be provided for this purpose.

#### Clinicians

Because the video and audio of telemedicine consultations will be recorded for retrospective analysis, informed consent will also be required from participating clinicians at both the PICU and regional referring hospitals. This process will be conducted by the investigators at commencement of the trial.

### Randomisation

Generation of intervention/control arm allocation sequences will occur centrally. Sequences will be generated using permuted block randomisation, with random block sizes of 6,8 or 10 entries and a 1:1 allocation ratio using an online true random number generation service [19]. The process of generating these sequences will be conducted by an independent party. Four tables of random numbers will be generated, one for each study site. Odd numbers will denote allocation to the control arm and even numbers to the intervention. The tables will be held securely on a server on a private network.

A password-protected custom application (accessible by computer or portable device), driven by the random number tables, will be provided for the PICU clinicians to determine cases and controls at time of initial retrieval call from RSQ. The application will record all accesses and allocations.

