### Sample size

In this study, resources limit the number of study sites to four and the study duration to 24 months. It is estimated that during the study period there will be 200 retrieval calls relating to eligible participants. We estimate an 80% participation rate (20% attrition due to lack of consent or clinicians electing not to consult by telemedicine and continuing by telephone) and consequently estimate the study will recruit a total of 160 retrieval participants with 80 in each arm. Retrospective stabilisation time data for the study sites showed a standard deviation of 41 minutes. With alpha = 0.05 we have 80% power to detect a clinically important difference in stabilisation time between-consultation types of 18 minutes or greater.

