**Table 2 Tab2:** **Statistical analyses for each outcome measure**

**Outcome measure**		**Statistical Method**
P1	Stabilisation time^1^	Linear regression with stabilisation time as the outcome, type of consultation as the main effect and PIM3 score as a co-variable
S1	Change in patient’s physiological status	Linear mixed effects model with physiological status as outcome, type of consultation and time as main effects, and a consultation-by-time interaction term.
S2	Change in diagnosis	Logistic mixed effects model with diagnosis as outcome, type of consultation and time as main effects, and a consultation-by-time interaction term.
S3	Destination of retrieved patients	Logistic regression with destination as outcome and type of consultation as the main effect.
S4	Retrieval decision	Logistic regression with retrieval decision as outcome and type of consultation as the main effect.
S5	PICU LoS^1^	Linear regression with LoS as the outcome, and type of consultation as the main effect.

^1^Data relating to stabilisation time and PICU LoS will transformed if necessary to meet assumptions of regression model.

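### Randomisation is stratified by site but the Table 2 models leave site out; if bedside time differs by site after PIM3, the primary test is conservative and some power is lost

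*Protocol article*

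**What the plan says.** The Randomisation section specifies "permuted block randomisation, with random block sizes of 6,8 or 10 entries and a 1:1 allocation ratio", and adds: "Four tables of random numbers will be generated, one for each study site". Site is therefore a stratification factor with four levels.

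Table 2 lists the model for each outcome:

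- P1 (stabilisation time): "Linear regression with stabilisation time as the outcome, type of consultation as the main effect and PIM3 score as a co-variable".
- S1 and S2 (physiological status, diagnosis): mixed models with "type of consultation and time as main effects, and a consultation-by-time interaction term".
- S3 (destination): "Logistic regression with destination as outcome and type of consultation as the main effect". S4 (retrieval decision) has the same form.
- S5 (PICU length of stay): "Linear regression with LoS as the outcome, and type of consultation as the main effect".

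No model contains site, and no other section adds it. The only stratification mentioned for analysis, under Primary outcome measure, is by initial risk (PIM3).

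On the sites, Study site selection states: "Site round trip distances from the RCH PICU range from 62 km to 1042 km". Table 1 gives the usual retrieval mode as road ambulance for one site, helicopter for one and fixed-wing aircraft for two. The Sample size section plans to "recruit a total of 160 retrieval participants with 80 in each arm", with a standard deviation of 41 minutes taken from retrospective data for the study sites.

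**The concern.** Blocking within site forces the arms to be nearly balanced within each site, so differences between sites largely cancel out of the treatment contrast. A model without a site term does not know this and counts between-site variation as residual noise. The reported standard error is then larger than the real sampling variability of the estimate, the confidence interval is wider than it need be, and the test rejects less often than its nominal level under the null.

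Table 2 goes as far as naming covariates: it puts PIM3 in P1 and nothing else. The missing site term is therefore a stated choice, not a detail left to an analysis plan that is not shown. The Sample size section says that resources fix the number of sites and the duration, so the sample cannot easily be enlarged. Precision that can be had without more patients is worth taking.

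**Working it through.** **Inputs.** From the Sample size section: 80 per arm, SD 41 minutes, alpha 0.05 (taken as two-sided, which reproduces the plan's figure), difference 18 minutes. The share of variance between sites, R², is not in the documents, so 0%, 5%, 10%, 20% and 30% are assumed. R² means the share of the variance left after PIM3, and 41 minutes is used as the SD of that remainder.

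**The plan's own figure.** SE = 41 × √(2/80) = 6.48 minutes. Power for 18 minutes = Φ(18/6.48 − 1.96) = 79.3%. Detectable difference at 80% power = (1.960 + 0.842) × 6.48 = 18.2 minutes. Exactly 80% power would need 82 per arm. The stated figure reproduces to rounding.

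**Effect of leaving site out.** With balance within site:

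- True SE = 6.48 × √(1 − R²), whether or not site is in the model.
- Reported SE without site stays at about 6.48; with site it matches the true SE.
- Type I error without site = 2 × [1 − Φ(1.96/√(1 − R²))].
- Power without site = Φ((18 − 1.96 × 6.48)/true SE).
- Power with site = Φ(18/true SE − 1.96).

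Example at R² = 20%: true SE = 6.48 × 0.894 = 5.80. Type I error = 2 × [1 − Φ(2.19)] = 2.8%. Power without site = Φ((18 − 12.71)/5.80) = Φ(0.91) = 81.9%. Power with site = Φ(3.10 − 1.96) = 87.4%.

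| Assumed R² | Type I error without site | Power without site | Power with site | Gain (points) | 95% CI half-width, without → with (min) |
|---|---|---|---|---|---|
| 0% | 5.0% | 79.3% | 79.3% | 0 | 12.7 → 12.7 |
| 5% | 4.4% | 79.9% | 81.3% | 1.4 | 12.7 → 12.4 |
| 10% | 3.9% | 80.5% | 83.3% | 2.8 | 12.7 → 12.1 |
| 20% | 2.8% | 81.9% | 87.4% | 5.5 | 12.7 → 11.4 |
| 30% | 1.9% | 83.5% | 91.3% | 7.8 | 12.7 → 10.6 |

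The detectable difference at 80% power without site is 1.960 × 6.48 + 0.842 × true SE. At R² of 10%, 20% and 30% this is 17.9, 17.6 and 17.3 minutes. With site it is 18.16 × √(1 − R²), that is 17.2, 16.2 and 15.2 minutes.

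**Simulation of P1.** Site-stratified blocks of 6, 8 or 10, four sites of 40 patients (equal size is an assumption), no PIM3 term, 8,000 runs. At R² = 20% without site: mean reported SE 6.48 against an actual SD of the estimate of 5.85, type I error 2.8%, power 81.4%. With site: SE 5.79, type I error 5.1%, power 86.9%. At R² = 0 the two analyses agree.

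**Simulation of a binary outcome.** Same allocation, 4,000 runs, log odds ratio 1.0 for power. The site event rates are assumed.

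| Site event rates | Type I error, without / with site | Power, without / with site | Mean SE of log OR under the null, without / with site |
|---|---|---|---|
| 30% at all four | 4.8% / 4.9% | 87.2% / 87.5% | 0.349 / 0.353 |
| 15, 25, 35, 45% | 4.2% / 4.9% | 82.2% / 84.5% | 0.349 / 0.364 |
| 10, 20, 50, 70% | 2.5% / 5.0% | 66.0% / 77.2% | 0.329 / 0.384 |

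Adding site restores the type I error and raises power, but the standard error of the odds ratio grows, because that odds ratio is now conditional on site.

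**S1.** The hypothesis is tested by the consultation-by-time interaction. A site main effect is the same at both time points, so it cancels from the within-child change. A simulation with two time points, 160 children and a large site effect gave an interaction SE of 0.2227 with and without site.

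**The case against.** The strongest objection is that the benefit is unknown and may be negligible. The primary outcome is bedside time, from the team's arrival to its departure, so it excludes travel. Distance and retrieval mode therefore do not establish that it differs by site. Study site selection describes all four as large regional public hospitals with an emergency department, a paediatric ward and paediatricians, and no section reports stabilisation time by site. PIM3 is already in P1 and may absorb differences in severity between sites. All of this stands. It is why the range starts at zero and why R² refers to what remains after PIM3. It does not remove the mismatch between design and analysis, and including site costs almost nothing if it proves unrelated to the outcome.

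Four stronger readings are tempting and should not be drawn:

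- **That the stated 80% power is wrong.** It reproduces, and under stratified allocation a site effect can only leave the power of the model without site where it is or raise it slightly.
- **That the gain is the distance from 79.3% to the adjusted figure** (4, 8 or 12 points at R² of 10%, 20% or 30%). The model without site also benefits from the balanced allocation, so the proper comparison gives about 3, 5 or 8 points.
- **That all six analyses lose precision.** The S1 interaction is unaffected by a site main effect, no gain is claimed for S2, and the logistic intervals in S3 and S4 do not narrow.
- **That the primary result is invalid.** The linear estimate is unbiased and type I error is not inflated; the error is on the conservative side.

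Adding the CEWT score at the initial call as a covariate in S3 to S5 would be a separate preference and forms no part of this point.

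**Conclusion.** The point holds in a limited form. The design stratifies by site and Table 2 omits it. Whether this costs anything depends on between-site variance in stabilisation time after PIM3, which the documents do not give. Over the assumed range of 0% to 30%, the loss in power for 18 minutes runs from nothing to about 8 points, and type I error without site falls from 5.0% to 1.9%. These figures assume near-balance within site and a post-PIM3 SD of 41 minutes. The same reasoning applies to S5, and to S3 and S4 as regards type I error and power for a site-conditional odds ratio. This is a change worth making, not a threat to validity.

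**What to change.** In Table 2, add site as a four-level fixed effect to P1 and S5. Add it to S3 and S4 where event counts allow, and state that the odds ratio is then conditional on site and that its interval is not expected to narrow. S1 and S2 need no change on this ground.

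The cost is a short edit to Table 2 and 3 degrees of freedom per model. Site is known for every patient, so no new data are needed. The edit should be made before outcomes are seen by arm. The sample size statement can stay as it is.

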### Masking

It is not possible to conceal study arm allocation from patients, clinicians or investigators. However data extractors will be masked, except when extracting audio and video related information which will be collected for the intervention arm only.

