### Patient recruitment

Patients will be recruited from the referring hospital paediatric wards, emergency departments or adult intensive care units.

Initial contact between the referring hospital clinician and RSQ will always be made by telephone (Figure 1). On receiving that call, the RSQ nurse co-ordinators, will then also contact the designated PICU consultant by telephone. Using the randomisation process, the PICU consultant will determine whether the consultation continues by telephone (usual care, control arm), or by telemedicine (intervention arm). While all parties will aim to comply with the study protocol, there may be circumstances under which the referring and PICU clinicians elect to override the randomisation process in the interest of the care of the child. The resulting loss of study cases will be monitored and recorded on a daily basis.

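### Opening the allocation is not expressly tied to confirmed consent, and children who stay on the telephone after allocation to telemedicine are counted as lost, against the stated intention-to-treat principle

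*Protocol article*

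**What the plan says.** On consent, the Patients section states: "Informed consent will be obtained from a parent or guardian by a clinician at the referring hospital before recruitment".

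On allocation, the Randomisation section provides a password-protected application that "will be provided for the PICU clinicians to determine cases and controls at time of initial retrieval call from RSQ". Of its contents it says only: "The application will record all accesses and allocations". The Patient recruitment section gives the sequence. The referring clinician telephones Retrieval Services Queensland (RSQ), RSQ telephones the PICU consultant, and then: "Using the randomisation process, the PICU consultant will determine whether the consultation continues by telephone (usual care, control arm), or by telemedicine (intervention arm"). The Masking section adds: "It is not possible to conceal study arm allocation from patients, clinicians or investigators".

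On losses, Patient recruitment allows the clinicians to override the randomisation in the interest of the child, and continues: "The resulting loss of study cases will be monitored and recorded on a daily basis". The Sample size section starts from this estimate: "It is estimated that during the study period there will be 200 retrieval calls relating to eligible participants". It then applies "20% attrition due to lack of consent or clinicians electing not to consult by telemedicine and continuing by telephone" to reach 160 recruited children, 80 per arm. The Data analysis section states the intention-to-treat principle without qualification.

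**The concern.** Two things are left loose.

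First, consent is taken by a clinician at the referring hospital, while the arm is revealed by a consultant at another hospital, reached through RSQ. The visible text does not say that consent status must reach the consultant before the application is opened. In an open trial that link should be explicit, because a child who is allocated and then found not to have consent leaves with the arm known.

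Second, two kinds of loss with different consequences share one figure. A child whose parent declines before allocation only makes the trial smaller. A child allocated to telemedicine whose clinicians stay on the telephone has already been randomised. Deducting that child from the number recruited removes someone from one arm for a reason that may be related to severity or urgency. The randomised groups are then no longer the groups compared, and the stated analysis principle is not being followed.

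**Working it through.** **The order of steps.** Patients places consent before recruitment. Patient recruitment is the heading under which both the RSQ call and the allocation are described. Read together, these put consent first. Neither Randomisation nor Patient recruitment says how the consultant learns that consent has been given. The gap is therefore an unstated link, not a stated reversal.

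**The plan's own figures.** Inputs from Sample size: 200 calls, 80% participation, SD 41 minutes, difference 18 minutes, alpha 0.05 (sidedness not stated; two-sided assumed).

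- 200 × 0.80 = 160, or 80 per arm.
- Standard error = 41 × √(2/80) = 6.48 minutes, and 18/6.48 = 2.78. Power = Φ(2.78 − 1.96) = 79.3%, against the stated 80%. The figures reproduce.

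**Splitting the 40 losses.** Let x of the 40 be children allocated to telemedicine who stayed on the telephone, and let the other 40 − x be non-consent before allocation. The number allocated is 200 − (40 − x) = 160 + x, or 80 + x/2 per arm. If the x children are excluded, the control arm keeps 80 + x/2 and the telemedicine arm keeps 80 − x/2. The stated 80 per arm is therefore the expected result only if x = 0, although the text names this second cause as part of the 20%. The documents do not give x, so the table shows its full range, with power for an 18-minute difference.

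| x | Allocated per arm | Analysed after exclusion (telephone v telemedicine) | Power |
|---|---|---|---|
| 0 | 80 | 80 v 80 | 79.3% |
| 20 | 90 | 90 v 70 | 78.7% |
| 40 | 100 | 100 v 60 | 76.7% |

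Power hardly moves. The issue is bias.

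**Form of the bias.** Let f be the share of the telemedicine arm excluded and D the difference in mean stabilisation time, excluded minus retained. The full-arm mean is the retained mean plus f × D, so exclusion shifts the comparison by f × D. With x = 20, f = 20/90 = 0.222. With x = 40, f = 40/100 = 0.40. Neither x nor D is in the documents, and D could have either sign. Purely as illustration:

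| x | D = 10 min | D = 20 min | D = 30 min |
|---|---|---|---|
| 20 | 2.2 min (type I error 6.3%) | 4.4 min (10.4%) | 6.7 min (17.5%) |
| 40 | 4.0 min (9.2%) | 8.0 min (22.3%) | 12.0 min (43.4%) |

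With x = 0 or D = 0 the shift is zero. These values ignore the planned PIM3 covariate, which would absorb part of any imbalance due to severity.

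**What keeping the children costs.** Assume that children who stay on the telephone gain nothing from their allocation, and that the effect in the others is 18 minutes. With x = 20, the intention-to-treat difference is 18 × 70/90 = 14.0 minutes and power with 90 per arm is 63%. With x = 40, it is 18 × 60/100 = 10.8 minutes and power with 100 per arm is 46%. If the difference stayed at 18 minutes, power would be 83.8% and 87.4%.

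**The case against.** A reader might infer that the arm is commonly revealed first, consent is sought afterwards, and children who decline are then dropped from the telemedicine arm. The documents do not support that. Consent is stated to come before recruitment, and the call and allocation are described under the recruitment heading. Allocation takes place at the later call, from RSQ to the PICU. The consultation then continues, which suggests that the referring clinician is already in contact and could report consent. Figure 1, the recruitment flowchart, is not shown and may contain the step. The article does not list the application's fields, and a condensed article need not do so. Falling from 200 calls to 160 participants is also compatible with non-consent before allocation. All of this stands, and it reduces the consent part to a request for an explicit sentence.

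On the losses, it can be said that intention to treat is stated, so overridden children may in fact be kept, and that the loss recorded daily may be only a monitoring count. That answer is weaker. The Sample size section subtracts these children before arriving at the number recruited, so as written they are not participants. The override clause in Patient recruitment does not say in which direction an override may go. Sample size does: away from telemedicine and onto the telephone.

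**Conclusion.** The point holds in two parts of unequal strength. The visible text does not link opening the allocation to confirmed consent. This is an ambiguity to close, not evidence that consent follows allocation. The stronger part is that the protocol treats children allocated to telemedicine but managed by telephone as lost study cases, and pools them with non-consent, while promising an intention-to-treat analysis. Followed as written, that removes children after allocation from one arm only.

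The resulting bias cannot be estimated from the documents. It depends on how many of the 40 expected losses are of this kind and on how those children differ from the rest, and neither is given. The minutes and error rates in the second table rest on assumed values and should not be quoted as an expected effect. The stated sample size and power are arithmetically sound.

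**What to change.** 1. In Randomisation and Patient recruitment, state that the consultant records confirmed consent before the application displays the arm, and that a call without it is logged as screened and not randomised. If Figure 1 already shows this, the text need only say so.
2. In Sample size, deduct only non-consent from the 200 calls, as a reduction before allocation. Give the expected rate of undelivered telemedicine separately, and restate the power with it.
3. In Patient recruitment, replace the notion of lost cases: every allocated child whose consultation was overridden or not delivered as assigned stays in the assigned arm for the intention-to-treat analysis, and non-delivery is reported by arm with reasons.

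The cost is one mandatory field in the application and a few sentences. Some calls without timely consent will not be randomised. Keeping undelivered cases may dilute the observed effect and, if non-delivery is common, reduce power, so the expected rate should be stated openly.
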